#### Concealment mechanism {16b}

During the process of obtaining informed consent (item 26a), patients will undergo several assessments, including the collection of survey data via the www.nettskjema.no, a 2-day polysomnography/home sleep testing, and a 7-day sleep diary alongside actigraphy recording. Importantly, both research assistants and patients will remain blinded to the specific study arm to which each patient will be assigned. The principal investigator (PI) will generate the entire randomisation sequence using the above RStudio syntax and inform patients/assistants about the group assignment when at least 12, or preferably 16, patients have been included in the study. Knowledge of the group assignment remains concealed until participants have passed baseline assessments.

### Implementation {16c}

After completing the baseline registrations, a research team member will inform each patient about study arm allocation, and notably, that those allocated to the TAU arm will receive the SleepWell condition after the four-month waiting period.

### Blinding

#### Who will be blinded after assignment to the intervention {17a}

The intervention’s specific characteristics preclude the blinding of therapists and patients. Participating patients will be fully informed about the study to ensure they understand and accept their assigned treatment arm. To prevent drop-out, TAU patients must understand that they will receive the SleepWell treatment approximately four months after their study inclusion (Fig. 1). Data analysts will be blinded by masking the group allocation, as will the research assistants collecting data, until all patients have completed the post-test assessment.

#### Procedure for unblinding if needed {17b}

Since blinding is not implemented in this trial, unblinding procedures are not applicable.

## Methods: data collection, management, and analysis

### Plans for assessment and collection of outcomes {18a}

The *primary outcomes* are measured by the following insomnia indicators:The Duke semi-structured clinical interview for deciding the presence of DSM-5 insomnia criteria [60, 61], and the Bergen Insomnia Scale (Five self-report items) for quantifying the dimensional level of DSM-5 insomnia nocturnal symptoms (sleep onset, maintenance and early awakening) and daytime consequences (poorer function in work, school or social life) that have lasted ≥ 3 months and occurred ≥ 3 nights a week [67]. The Duke interview also probes for other sleep disorders regarding patient exclusion, notably restless legs or sleep apnoea.Actigraphy (Actiwatch Spectrum Plus, Phillips Respironics) worn on the non-dominant arm, providing estimates of physical activity level, light exposure, SOL, duration of wake time during the nights, WASO and EMA. In addition, sleep continuity is calculated as the proportion of time in bed spent sleeping (SE %: sleep efficiency). Recordings will be performed for 7 days, and an average of the sleep indices will be calculated.The sleep diary will be manually completed every morning concerning the last night’s sleep and every evening concerning daytime fatigue or sleepiness. The diary will be used to complement the scoring of the actigraphy recordings.The *secondary outcomes* are measured by the following:A simplified PSG, i.e. the Home Sleep Test REM + (HST) (Somnomedics Randersacker Germany, GmhB), is used to complement actigraphy with sleep architecture assessments at nights 1–3 and REM sleep, arousals and sleep stage shifts. The HST can be used at home, allowing patients to hook up the equipment themselves. The device records 11 signals (3 frontopolar, 2 EOG, 1 EMG, snoring (sound), light in the room, movement, head position, continuous impedance measurement (signal quality), finger plethysmograph with oxygen saturation, heart rate and movement). We will evaluate whether patients receiving the SleepWell intervention attain a higher proportion or longer duration of slow-wave (N3) than light-wave (N1, N2) sleep than TAU patients and whether they attain a reduction in the arousal index or sleep stage index indicative of sleep disturbance. The recording will be made two nights per patient due to the “first night effect” related to habituation [68]. However, since the HST is less intrusive to wear and sleep with at home than a full PSG, the average of both nights will be used.The Hospital Anxiety and Depression Scale (HADS, 14 items) is designed for hospital populations as it rates the degree of non-vegetative symptoms of depression (7 items) and anxiety (7 items). Item scores range from 0 to 3, and total scores range from 0 to 21 for each subscale [69]. It is widely used as a screening instrument, and a HADS score ≥ 8 is used as a diagnostic marker [70] in Norway.The EQ-5Q-5L is a broad quality-of-life index covering the domains of mobility, self-care ability, daily activity function, pain/discomfort and affective symptoms [71].The Chalder Fatigue Scale (11 items) measures the degree of physical (7 items) and mental exhaustion (4 items) [72]. Each item is scored from 0 to 3 (total range, 0–33), with higher scores indicating more fatigue.The Brief Pain Inventory (BPI, 11 items) indexes pain intensity and interference, as well as body localisation of pain [73].

The qualitative, semi-structured interviews will be conducted to explore the feasibility and acceptability of the intervention from the participants’ perspective. To ensure variability in the participants’ experiences, we plan to use self-reported insomnia symptoms at post-test to invite a comparable number of patients with varying treatment responses, ranging from favourable to less favourable. Patients who drop out or withdraw during the intervention will also be invited to participate in the interviews. The interviews will be in person or via telephone, based on the participant’s preferences. The Nettskjema service also includes a dictation application that will be used to audio record the interviews before they are transcribed verbatim for analysis.

### Plans to promote participant retention and complete follow-up {18b}

During recruitment, patients will receive detailed information about the purpose of the study, the randomisation and the requirements related to the intervention. To promote patient retention, baseline registrations will be conducted before the randomisation. Using the “*Nettskjema*” survey platform to collect the questionnaire data may provide a level of flexibility and convenience for the participants, thus reducing the risk of missing data. Nevertheless, patients considered eligible and who consent to participate have the option of unconditional withdrawal; if so, they will suffer no consequences for further medical treatments. In line with the intention-to-treat approach, patients who drop out or withdraw from the study after collecting baseline data will be included in the final analyses unless they have withdrawn their consent. Patients who drop out or withdraw during the intervention will also be invited to participate in the planned qualitative interviews to explore their experiences of treatment feasibility and acceptability.

### Data management {19}

The study complies with the General Data Protection Regulation (Ch. 2, Art. 6/pt. 1e and Art. 9/pt. 2j) and the institutional data management and storage guidelines set by UiT–The Arctic University of Norway. All patient data will be stored in a de-identified form. Data collected during a night’s sleep by the Home Sleep Test REM + device will be uploaded to a web-based service by Somnomedics (using Microsoft Azure server setup) for automated scoring of the polysomnogram, thereafter downloaded to the Microsoft Office365 Sharepoint service hosted by the UiT–The Arctic University of Norway for revision by a clinical neurophysiologist/somnologist. The actigraphy recordings will be uploaded directly to the UiT Office365 Sharepoint service. Survey- and qualitative data are collected/registered through https://nettskjema.no and will be managed digitally using the Service for Sensitive Data (TSD) (a secure service for sensitive data managed by the University of Oslo), which ensures data integrity. After completing the data collection process, the data are transferred to the UiT Microsoft Office365 Sharepoint server. Data access is restricted to the PI, who may authorise access to project members. The Sharepoint service has a 30-day file version history with regular backup routines.

### Statistical methods for primary and secondary outcomes {20a}

Patients randomly assigned to the waiting list (WL) group will conduct two baseline measurements separated by ~ 4 months, with the second one serving as the comparator to the post-test for the SleepWell groups. WL patients then cross over to the SleepWell intervention (Fig. 1) and follow the same plan for post-test and follow-up measurements as the SleepWell study arm.

The primary hypothesis examines the mean group difference between the SleepWell post-test status for all patients receiving treatment and the second baseline status of the WL patients having only received TAU. Since this test involves only two repeated measurements, a conventional analysis of covariance is used with the baseline value of the outcome added as a covariate. Designating baseline values as covariates has become standard practice in therapy research as it improves the precision of the mean difference estimate [80], which also improves the statistical power [81] in estimating the hypothesised mean group difference (0-SleepWell, 1-TAU).

Generalised linear mixed regression models are preferred due to the flexibility in managing most variables (continuous, binary, counts, etc.) and data clustering. Here, some degree of clustering may occur between individuals in the same therapy group as they share a common therapy climate (fellow group patients and therapists), which may underestimate the standard errors and increase the risk of a type 1 error in hypothesis testing. The effect of this nesting will be managed by adding the group number as a random factor.

The GenLinMixed models for the later follow-up tests are comparable, except they add a random intercept factor in addition to the baseline adjustment to account for any leftover correlations in the repeated data, which adjusts the error bands appropriately. Because all patients have received treatment at follow-up, direct testing of general treatment–control effects at follow-up is irrelevant (the *Group* factor). The estimable fixed factors thus become *Time* (1-post, 2-follow-up at 4 months and 3-follow-up at 12 months) and the *Time*Group* interaction that allows mean group differences at different time points. We will analyse if relapse occurs during the follow-up period by conducting repeated time series contrast analyses. In case of significant contrasts indicative of relapse, we will examine for possible differences between the SleepWell (early treatment) and the TAU (late treatment) study arms. Effect size statistics will be given as a standardised mean difference by dividing the beta-weight for a group comparison or a time difference with the within-subject standard deviation for the test, i.e. the residual SD.

The analyses will be conducted conservatively as intention-to-treat. Alpha values < 0.05 and 0.01 are assumed for the hypotheses about primary sleep treatment outcomes, i.e. SOL, WASO, SE and EMA, and secondary outcomes, i.e. affective health, fatigue and quality of life, respectively. The alpha value is set to 0.01 for analyses of moderators and mediators. The GenLinMixed handles missing data adequately without the need for multiple imputations, as it estimates the parameters based on all data available [82], thus reducing biases related to dropout given a missing-at-random (MAR) dropout pattern.

Since moderator variables in CBT-i are imperfectly understood [83], exploratory moderator analysis will extend the above regression models by adding the moderator variable with its two-way interactions with Time and Group to get a full three-way interaction that may discern exactly the subgroups defined by the moderator that benefit the most from treatment.

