### Eligibility criteria {10}

Eligible are patients aged 18–75 years with a chronic non-malignant pain condition as defined by the International Association for the Study of Pain (IASP) [59], and who meet the DSM-5 criteria for comorbid insomnia [1] determined by the Duke structured clinical interview [60, 61].

Exclusion criteria are (1) a comorbid drug abuse diagnosis, (2) involvement in ongoing compensation and/or insurance cases related to their current or previous health or treatment, (3) a current medical treatment using over 100 mg oral morphine equivalents, (4) a current involvement in other psychological treatments for pain and/or insomnia, (5) admittance to hospital psychiatric treatment during the past 12 months, (6) an epilepsy diagnosis, (7) poor Norwegian communication skills or (8) suffering from restless legs or sleep apnoea.

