### Outcomes {12}

The overall hypothesis is that the SleepWell intervention will outperform TAU. This will be tested using the following primary (A) and secondary (B) outcome measures:

(A)Favourable changes in the DSM-5 insomnia criteria (1) related to nocturnal symptoms (i.e. SOL-sleep onset latency, WASO-wake after sleep onset, EMA-early morning awakening) and daytime functioning (e.g. reduced dissatisfaction with nighttime sleep and fewer functional problems in education, work or social life). This is assessed with different classes of insomnia measures, i.e. the semi-structured Duke clinical interview for insomnia [60, 61], and the DSM-5 adapted Bergen Insomnia Scale (BIS) [67]. Comparable nocturnal improvements in SOL, WASO and EMA are registered across 7 days using an actigraphy recording device, while the sleep diary complements the actigraphy data. The clinical assessment process for diagnosing insomnia is primarily based on patients’ subjective reports. Thus, the SleepWell intervention will be considered efficacious if it results in a significant reduction in self-reported insomnia symptoms, as measured by the BIS, or in the proportion of individuals who satisfy the criteria for an insomnia diagnosis. Concomitant reductions in nocturnal sleep symptoms, as measured with the actigraphy/sleep diary, will broaden the support of the SleepWell.

(B)Improvements in objectively measured sleep with the “Home Sleep Test” device in terms of an increased proportion and duration of slow-wave sleep, reduced sleep fragmentation and fewer sleep disruptions due to EEG-based microarousals. Secondary measures also include reductions in patient-reported depression and anxiety, pain intensity and interference, fatigue and use of sleep medication, and improvements in pain acceptance and quality of life.

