### Participant timeline {13}

The timeline for participant recruitment, intervention delivery and assessments is outlined in Figs. 1 and 2. After initial screening and confirmation of eligibility, participants will complete baseline assessments before randomisation. The intervention group will begin the SleepWell programme immediately, while the comparison group will continue TAU. Assessments will occur at the following intervals:Baseline (Week 0): Comprehensive evaluations using the Duke sleep interview for insomnia, sleep diaries, actigraphy, PSG/Home Sleep Test REM and self-report psychological instruments related to primary and secondary outcome variables, including mediation variables.Post-Intervention (Week 16): Assessment of short-term outcomes in SleepWell group, and second baseline measurement of the TAU group. The measurements are similar to those collected at baseline (week 0), in addition to qualitative interviews with the participants’ experiences of receiving the intervention.Post-Intervention for TAU (Week 32): This assessment is conducted after the TAU group has received the SleepWell intervention. The assessments are similar to those used at the post-intervention at week 16.Follow-Up Assessments: These are conducted 4 and 12 months after the post-test to evaluate maintenance of treatment effects. This is planned for weeks 32 and 64 in the SleepWell study arm and weeks 48 and 80 in the TAU arm. Self-report data are collected at the first follow-up test. At the final follow-up, both self-report data and actigraphy data are collected.

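### The Duke diagnosis can establish efficacy alone, but it is an entry requirement, so adjusting it for its own baseline value cannot work and no other covariate is named

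*Protocol article*

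**What the plan says.** - **Entry.** Eligibility criteria {10} takes patients "who meet the DSM-5 criteria for comorbid insomnia [1] determined by the Duke structured clinical interview".
- **Endpoint.** Plans for assessment and collection of outcomes {18a} lists as a primary outcome "The Duke semi-structured clinical interview for deciding the presence of DSM-5 insomnia criteria", a yes/no result. The BIS stands beside it "for quantifying the dimensional level of DSM-5 insomnia nocturnal symptoms".
- **Success rule.** Outcomes {12} calls the intervention efficacious on a significant fall in the BIS "or in the proportion of individuals who satisfy the criteria for an insomnia diagnosis". Either is enough.
- **Timing.** Participant timeline {13} places the week-0 measurements after confirmation of eligibility and describes them as "Comprehensive evaluations using the Duke sleep interview for insomnia, sleep diaries, actigraphy" and further instruments, including the self-report measures for the primary outcomes.
- **Analysis.** Statistical methods {20a} says for the primary hypothesis that "a conventional analysis of covariance is used with the baseline value of the outcome added as a covariate", and justifies this by precision and power. The next paragraph adds: "Generalised linear mixed regression models are preferred due to the flexibility in managing most variables (continuous, binary, counts, etc.) and data clustering". It names no other baseline covariate for a binary outcome.

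**The concern.** A baseline covariate helps only if it differs between patients and predicts the outcome. The Duke diagnosis is required for entry, so its baseline value separates nobody. The one adjustment rule given for the primary test therefore cannot be carried out usefully for one of the two results that can decide the trial.

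Two things are at stake. The first is precision: a graded severity score is collected at week 0 and would go unused for this endpoint. The second is discretion: an analyst who finds the covariate inestimable must either drop it or choose a substitute. Blinding {17a} masks analysts only until all patients have completed the post-test, so that choice could be made with allocation known.

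**Working it through.** **1. The covariate.** Inputs: 106 patients, 53 per arm (Sample size {14}); Duke diagnosis present in all at entry ({10}). The model columns are intercept (all 1), group (0 or 1) and baseline diagnosis (all 1). That is three columns with rank 2: the third duplicates the first, its coefficient is not estimable, and it explains 0% of the variance. If the week-0 interview is a second one and a few patients no longer qualify, the column varies slightly but still carries almost no information.

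**2. The protocol's own figure.** {14} uses d = 0.60, pre-post correlation 0.5 (R² = 0.25), alpha 0.05 and power 0.80.
- Residual SD = √(1 − 0.25) = 0.866, so the working effect is 0.60 / 0.866 = 0.693.
- Noncentral t with N − 3 degrees of freedom, two-sided: N = 68, power 0.803. This matches.
- Design effect: 1 + (6 − 1) × 0.05 = 1.25, and 68 × 1.25 = 85. This matches.
- Dropout: 85 / 0.8 = 106.25, stated as 106.

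The figure is sound for a continuous outcome with a varying baseline. Its R² = 0.25 has no counterpart for the Duke diagnosis under own-baseline adjustment.

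**3. What a usable covariate would add.** The documents give no diagnosis rates, so those below are assumptions.
- Patients: 106 × 0.8 = 84.8, taken as 84 (42 per arm), clustering ignored.
- Model: baseline severity X and week-16 latent severity Z are normal with correlation ρ. The diagnosis is present when Z passes an arm-specific cut that gives the assumed rate.
- Test: logistic regression on arm, with and without X; 3,000 simulated trials per row.

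| Still diagnosed, TAU v SleepWell | ρ | Unadjusted power | Adjusted power | Gain (points) |
|---|---|---|---|---|
| 80% v 50% | 0.3 | 0.851 | 0.864 | 1.3 |
| 80% v 50% | 0.5 | 0.836 | 0.884 | 4.8 |
| 80% v 50% | 0.6 | 0.829 | 0.903 | 7.4 |
| 70% v 40% | 0.3 | 0.792 | 0.813 | 2.1 |
| 70% v 40% | 0.5 | 0.801 | 0.860 | 5.9 |
| 70% v 40% | 0.6 | 0.803 | 0.886 | 8.3 |

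Unadjusted power does not depend on ρ, so its spread within a scenario is simulation error (standard error about √(0.84 × 0.16 / 3000) = 0.007). Allowing for repeat runs, the gains are about 1–2 points at ρ = 0.3, 4–6 at 0.5 and 6–8 at 0.6. At ρ = 0.2 the gain was under 1 point.

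**4. Validity.** With 65% still diagnosed in both arms, 42 per arm and 8,000 trials, type I error was 4.7% unadjusted and 4.5% adjusted.

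**The case against.** The strongest reply is that the covariance sentence in {20a} is about means. The hypothesis there is a mean group difference, and the precision claim refers to that difference. Binary outcomes appear only in the mixed-model paragraph, which states no covariate. The statistical section's own list of primary outcomes is sleep onset latency, wake after sleep onset, sleep efficiency and early morning awakening, all with baselines that vary. This stands in part: that the rule covers the Duke endpoint is an inference, not explicit text. It is a reasonable one, because the rule is given for the primary hypothesis, {12} and {18a} make the diagnosis primary, and {20a} carries the baseline adjustment into the follow-up mixed models. No other baseline covariate is offered for the primary test. {20c} allows further covariates only where they relate to missingness.

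A reader might infer more than the documents support:
- **That the comparison is biased.** It is not. Allocation is randomised, and dropping a constant leaves a valid comparison of proportions. Chance imbalance in severity costs precision only.
- **That every baseline value is certainly positive.** {13} does not say whether the week-0 Duke interview is the eligibility interview or a second one. Constant or nearly constant is as far as the text goes.
- **That the sample size is wrong.** Setting R² to 0 in the protocol's formula gives 90, then 113, then 142. But that formula is in Cohen's d and never covered a binary endpoint, so these numbers are not a requirement for it.
- **That 0.5 is the protocol's figure for this gain.** It is a pre-post correlation from a Cohen's d calculation. The correlation of self-reported BIS with a later interview diagnosis, in patients selected for insomnia, may be lower.

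An unadjusted comparison of proportions is also a legitimate analysis. It should then be stated as the choice.

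**Conclusion.** The point holds in a limited form. Own-baseline adjustment cannot work for the Duke diagnosis, which can establish efficacy alone, and the only baseline covariate named for the primary test is that unusable one. The effect is lost precision, not bias or an inflated error rate. It is worth between about 1 and 8 points of power over correlations of 0.3 to 0.6, given the assumed rates, 84 patients and no clustering. Adjustment of the BIS and the actigraphy outcomes is unaffected. The change is worth making because the rule as written is unworkable for this endpoint and the better covariate is already collected.

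**What to change.** In {20a}, prespecify that the binary mixed model for the Duke diagnosis uses the baseline BIS total score as covariate, because the baseline diagnosis is fixed by eligibility. Keep own-baseline adjustment for the BIS and the actigraphy outcomes. Do not carry the R² of 25% in {14} over to the diagnosis endpoint.

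The cost is a sentence or two before unmasking. The BIS is already collected at week 0 in both arms, so there is no new visit, instrument or patient burden. There is one small downside: the adjusted odds ratio is conditional on baseline severity, whereas the success rule in {12} concerns proportions. The difference in proportions should therefore be reported alongside it, for example by standardising the model's predictions over the trial sample.

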### Sample size {14}

A meta-analysis of comparable somatic diagnoses (5 studies) indicated a standardised mean difference (Cohen’s *d*) between intervention and control ranging between 0.60 and 0.80 [18]. With randomisation done on an individual level, a correlation = 0.5 between pre- and post-test (R-sq = 25%), alpha = 0.05, power = 0.80 and minimum Cohen’s *d* = 0.60, at least *N* = 68 patients are required to reject the null hypothesis. With an estimated intra-class correlation (ICC) = 0.05 (adjustment for similarities that occur between patients due to sharing of a treatment group, cluster size = 6), which yields a design effect of 1.25 (1 + (6–1)*ICC), at least *N* = 85 participants are needed. Adding a safety margin of 20% dropout means a final sample estimate of *N* = 106 patients (*n* = 53 SleepWell, and *n* = 53 TAU).

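### At the week-16 primary contrast only SleepWell patients are in therapy groups, but the design effect is applied to both arms and the random group term is not limited to SleepWell

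*Protocol article*

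**What the plan says.** **Sample size {14}.** The plan takes "alpha = 0.05, power = 0.80 and minimum Cohen’s *d* = 0.60", a pre–post correlation of 0.5, and concludes that "at least *N* = 68 patients are required to reject the null hypothesis". It then brings in clustering "With an estimated intra-class correlation (ICC) = 0.05", described as "adjustment for similarities that occur between patients due to sharing of a treatment group", with cluster size 6. The resulting factor of 1.25 multiplies all 68 patients to give 85, and a 20% dropout allowance gives 106 (53 per arm).

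**Statistical methods for primary and secondary outcomes {20a}.** The primary hypothesis compares the SleepWell post-test with the second baseline of waiting-list patients, who up to then have had TAU only. For this test, "a conventional analysis of covariance is used with the baseline value of the outcome added as a covariate". The next paragraph prefers generalised linear mixed models, explains that patients in the same therapy group may resemble one another, and states: "The effect of this nesting will be managed by adding the group number as a random factor".

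**Who is in a group, and when.** Intervention descriptions {11a} places 6–8 patients in each SleepWell group. Explanation for the choice of comparators {6b} describes TAU as unsystematic care from the pain clinic or GP. Under Participant timeline {13}, TAU patients cross over to SleepWell about four months after baseline, that is, after the measurement used in the primary test.

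**The concern.** At the primary time point one arm is clustered and the other is not. The ICC is justified by shared treatment groups, yet the arithmetic inflates the arm that has none, so the sample-size statement does not describe the design.

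In the analysis, a random factor needs a level for every patient, and at week 16 a TAU patient has no therapy-group number. The text neither confines the factor to SleepWell nor says what TAU patients receive. It also stands beside an analysis of covariance which, read literally, has no such factor. The standard error of the primary test therefore depends on a choice that the wording leaves open.

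**Working it through.** **Inputs (Sample size {14}).** d = 0.60, r = 0.5, alpha 0.05 (two-sided reproduces the plan's figure), power 0.80, ICC 0.05, cluster size 6, dropout 20%. Group size up to 8 comes from Intervention descriptions {11a}. Assumption: the ICC applies to the baseline-adjusted outcome, as the plan's multiplication implies.

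**1. The plan's own chain.**
- Adjusted variance: 1 − 0.5² = 0.75.
- Two-sample noncentral-t calculation: 34 per arm, N = 68, power 0.803.
- Design effect: 1 + (6 − 1) × 0.05 = 1.25, and 68 × 1.25 = 85.
- Dropout: 85 / 0.80 = 106.25, stated as 106.

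The chain reproduces, but only with 1.25 in both arms.

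**2. Clustering in SleepWell only.** The variance of the difference is proportional to 1.25/n + 1/n, so the average inflation is (1.25 + 1)/2 = 1.125.
- Groups of 6: 68 × 1.125 = 76.5, so 77, or 78 in equal arms. Recruited: 76.5/0.80 = 95.6 to 78/0.80 = 97.5, about 96–98.
- Groups of 8: design effect 1.35, average 1.175, 68 × 1.175 = 79.9, so 80. Recruited: 100.
- An average of 1.25 with one-arm clustering would need ICC = 0.10.

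**3. Power at 42 analysed per arm (7 groups of 6).**
- SE² = 0.75 × (1.25 + 1)/42 = 0.0402, so SE = 0.200.
- Normal approximation: Φ(0.60/0.200 − 1.96) = 0.85.
- Satterthwaite df, with 6 df for the SleepWell mean and 41 for the TAU mean: 0.0402² / (0.0223²/6 + 0.0179²/41) ≈ 18.

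| Analysed per arm | Group size | Normal | Satterthwaite df |
|---|---|---|---|
| 42 | 6 | 0.85 | 0.81 (df about 18) |
| 42 | 8 | 0.83 | 0.77 (df about 12) |
| 39 | 6 | 0.82 | 0.77 (df about 16) |

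The last row shows that the corrected 78 evaluable patients would fall short of 0.80 once the small number of groups is allowed for. The surplus in the stated N is largely used up in this way.

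**4. How the TAU coding affects the test (42 per arm, ICC 0.05).**
- *Each TAU patient unclustered:* SE 0.200, as above.
- *All TAU patients under one code:* SE² = 0.75 × (2 × 0.95/42 + 0.05/7 + 0.05) = 0.0768, so SE = 0.277. The ratio is 0.277/0.200 = 1.38, and power is Φ(0.60/0.277 − 1.96) = 0.58. At 53 per arm the ratio is 1.47 and power 0.63.
- *TAU patients given their later group numbers:* SE about 1.05 times the correct value.
- *Groups ignored (plain ANCOVA):* the true SE exceeds the model SE by √1.125 = 1.061, so the type I error is 2 × [1 − Φ(1.96/1.061)] = 6.5%. At ICC 0.10 the factor is √1.25 and the error about 8%.

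Simulation agrees: power 57% with one TAU code, and type I error 6.8% (ICC 0.05) and 8.3% (ICC 0.10) when groups are ignored.

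**The case against.** **The analysis section is not blind to clustering.** It ties clustering to shared therapy groups, warns about type I error, and describes the follow-up mixed models as comparable to the primary one apart from an added random intercept. The best reading is a baseline-adjusted mixed model with a group term, the word *conventional* being loose. This stands. A reader might infer that the trial will ignore clustering and run at 6.5–7% type I error; the text does not support that, and the figure shows only what a literal ANCOVA would cost.

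**The coding may be in an SAP that is not shown.** This also stands for coding detail and for the degrees-of-freedom method, on which the article is silent. The one-code case is a possible coding, not a stated one, so power of 0.58 is not a forecast. Leaving the group number blank could drop the whole comparator arm, which would be noticed at once. What an SAP would not change is the design-effect step, and the article itself sets an unrestricted group factor beside a model without one.

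**The sample-size error is conservative.** Agreed. A reader might infer that the trial is too small; the calculation shows the opposite, by about 8–10 recruited patients.

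**Scope.** After crossover every treated patient has a therapy group, so the follow-up models are not affected.

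**Conclusion.** The point holds for the week-16 primary contrast. The design effect of 1.25 belongs to SleepWell only; averaged over the arms it is 1.125, so 77–78 evaluable patients correspond to the plan's stated power, not 85. N = 106 is not too small on this account: with 84–85 evaluable, power is about 0.85 by normal approximation and about 0.81 with small-sample degrees of freedom, falling to about 0.77 if groups reach 8. The analysis wording needs closing because permissible readings run from a mildly liberal test to one with a standard error about 1.4 times too large. These figures assume ICC 0.05 on the adjusted outcome, equal group sizes and equal arms. They do not show that the trial is underpowered or that its primary test will be invalid.

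**What to change.** Keep N = 106.

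1. **Sample size {14}:** apply the design effect to the SleepWell arm only and state the resulting power, with small-sample degrees of freedom and for groups of 6 and of 8.
2. **Statistical methods {20a}:** define the primary test as a baseline-adjusted (generalised) linear mixed model, for whichever primary outcome is analysed, with a random therapy-group effect for SleepWell patients only. Treat each TAU patient as unclustered or as a singleton. For continuous outcomes allow arm-specific residual variance, and use Satterthwaite or Kenward–Roger degrees of freedom.
3. Reconcile the analysis-of-covariance sentence with that model.

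This leaves open which primary outcome leads. Outcomes {12} accepts either the Bergen Insomnia Scale or the proportion meeting diagnostic criteria, and that is a separate question.

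The cost is wording in two sections and slightly wider intervals. No extra patients or data are needed. The change should be made before allocation is unmasked to the analysts.
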